# Oral nicotinamide mononucleotide (NMN) to treat chronic insomnia: protocol for the multicenter, randomized, double-blinded, placebo-controlled trial

**DOI:** 10.1186/s13063-023-07351-8

**Published:** 2023-05-18

**Keywords:** Chronic insomnia, Nicotinamide mononucleotide (NMN), Randomized controlled trial

## Abstract

**Background:**

The treatment of insomnia, which is the most common sleep disorder, includes drug and behavioral treatment, but each treatment measure has its limitations. So new treatment method needs to be taken to improve the treatment effect. MN supplementation is a potential promising new method for the treatment of insomnia, resulting in a rising need for methodological research towards verifying its efficacy.

**Methods/design:**

We describe a proposal for a multicenter, patient-assessor-blinded, randomized controlled trial with two parallel arms. A total of 400 chronic insomnia patients will be allocated 1:1 to the intervention group (treatment with oral NMN 320 mg/day) or control group (treatment with oral placebo). All subjects are clinical chronic insomnia patients who meet all inclusion criteria. All subjects are treated by taking NMN or placebo.

The primary outcome is the score on the Pittsburgh Sleep Quality Index (PSQI). Secondary outcomes are the score on the Insomnia Severity Index (ISI) and Epworth Sleeping Scale (ESS), the total sleep time (TST), sleep efficiency (SE), sleep latency, and REM sleep latency to assess sleep quality changes.

Subjects are assessed at two time points: baseline and follow-up. The duration of the clinical trial is 60 days.

**Discussion:**

This study will provide more evidence on the effects of NMN on improving sleep quality among patients with chronic insomnia. If proven effective, NMN supplement can be used as a new treatment for chronic insomnia in the future.

**Trial registration:**

Chinese Clinical Trial Registry (chictr.org.cn) ChiCTR2200058001. Registered on 26 March 2022.

Name and contact information for the trial sponsor {5b}	This trial is funded and proceeded by China Health Promotion Foundation [name], [name], [name], Email: [name]
Role of sponsor {5c}	This trial is solely funded by non-commercial sources. Funding sources have had no role in the design of this study and will not have any role during its execution, analyses, interpretation of the data, or decision to submit results

**Table 2 Tab2:** Registration data

Data category	Information
Primary registry and trial identifying number	ChiCTR2200058001
Date of registration in primary registry	March 26, 2022
Secondary identifying numbers	NA
Source(s) of monetary or material support	China Health Promotion Foundation
Primary sponsor	China Health Promotion Foundation
Secondary sponsor(s)	NA
Contact for public queries	[name] (Email: [name])
Contact for scientific queries	[name] (Email: [contact])
Public title	Oral nicotinamide mononucleotide (NMN) as a treatment for chronic insomnia: protocol for the multicenter, randomized, double-blind, placebo-controlled trial
Scientific title	Oral nicotinamide mononucleotide (NMN) as a treatment for chronic insomnia: protocol for the multicenter, randomized, double-blind, placebo-controlled trial
Countries of recruitment	China
Health condition(s) or problem(s) studied	Chronic insomnia
Intervention(s)	Active comparator: Nicotinamide mononucleotide (320 mg/day) Placebo comparator: Placebo
Key inclusion and exclusion criteria	Inclusion criteria: Age between 18 and 65 years; clinical diagnosis of chronic insomnia (according to the ICSD-3 criteria for chronic insomnia)
	Exclusion criteria: Physical diseases, mental disorders, and/or sleep disorders; received any insomnia drugs and psychotherapy within the preceding 1 month; on a continuous current daily intake of nutritional supplements and vitamin supplements
Study type	Interventional
	Multicenter, double-blinded, randomized controlled superiority trial with a two-group parallel design
	Phase III
Date of first enrolment	April 2022
Target sample size	400
Recruitment status	Recruiting
Primary outcome(s)	Pittsburgh Sleep Quality Index (PSQI)
Key secondary outcomes	Epworth Sleeping Scale (ESS), Insomnia Severity Index (ISI), Total sleep time (TST), sleep efficiency (SE), sleep latency, REM sleep latency, the percentage of N1, N2, N3, and REM

## Introduction

### Background and rationale {6a}

#### Insomnia

Insomnia refers to persistent challenges in falling asleep, maintaining sleep, or waking up earlier than the habitual rise time, and is associated with the impairment of daytime functioning despite the opportunity for sufficient sleep duration [1]. It is a prevalent condition associated with significant morbidity, reduced productivity, increased risk of accidents, and poor quality of life [2]. The prevalence of insomnia disorder is approximately 10–20%, of which approximately 50% have a chronic course [3]. Based on a meta-analysis of China’s population, the prevalence of insomnia was 15% [4]. Of the Chinese survey respondents, 45.4% reported varying degrees of insomnia [5]. Insomnia has become the second major reason that leads patients to visit neurology clinics, the first one is headaches [6]. Owing to its prevalence, the annual loss of quality-adjusted life-years (QALYs) from insomnia appears to be greater than that from other medical and psychiatric conditions, including arthritis, depression, and hypertension [7]. As the most common sleep disorder, insomnia is a substantial burden on healthcare systems and vulnerable patient groups. The combined direct and indirect costs for insomnia in the United States exceed $100 billion annually [8].

Currently, the prescribed treatment for insomnia primarily involves drug and behavioral treatments, however, they have limitations [9]. Many patients prefer hypnotics to non-drug treatments despite side effects and issues with drug dependence and tolerance because they help reduce sleep latency (SL) and increase total sleep time (TST) at night [10, 11]. Multifactorial behavioral treatments such as cognitive behavioral therapy for insomnia (CBTI) have moderate to great effects on sleep parameters; however, only 26–43% of patients experience complete relief from insomnia [12]. Moreover, the high cost and lack of trained providers of CBTI have prevented widespread uptake [13–15]. Therefore, the public health burden of insomnia is still large, and new treatment methods must be developed to improve it.

Insomnia is a complex interaction between psychological cognitive arousal, altered circadian clock, and sleep homeostatic mechanisms. Circadian factors promote wakefulness on a roughly 24-h biological clock, whereas homeostatic factors respond to accumulated wakefulness with the drive for sleep [16, 17]. Disrupted sleep–wake and molecular circadian rhythms are features of aging associated with metabolic diseases and reduced nicotinamide adenine dinucleotide (NAD +) levels [18]. A clue to the mechanism underlying the decline in circadian rhythms and metabolism with age stems from the observation that the longevity-associated deacetylase, SIRT1, interacts with the core clock complex [19, 20]. For SIRT1 activity to occur, the sentinel metabolite NAD + , which declines with age is required. Declining NAD + /SIRT1 leads to the downregulated expression of clock genes, such as BMAL1 and PER2, which affects the internal circadian clock [21–23]. Neural activation dependent on SIRT1 in the dorsomedial hypothalamic nucleus and lateral hypothalamus has been reported to prevent aging-induced decline in the quality of sleep-in mice [24]. Nicotinamide mononucleotide (NMN) is an intermediate that effectively improves the level of NAD + [22] and has been extensively studied over the years [25]. Therefore, NMN supplementation is a promising method to treat insomnia. Recent preclinical studies have demonstrated that administering NMN could compensate for NAD + deficiency and can affect diverse pharmacological activities in various diseases, including diabetes, obesity, ischemia reperfusion injury (IRI), and heart failure [26–29]. Given that NMN has demonstrated high efficacy and benefits in various mouse models of human disease, several clinical trials have been conducted to investigate its clinical applicability [30, 31]. Therefore, it is necessary to verify the of NMN’s effect on insomnia. This trial aims to prove that NMN supplementation is an effective treatment for therapy chronic insomnia, a subtype of insomnia, and refers to symptoms occurring 3 or more times per week for 3 months or longer [16].

### Objectives {7}

Our primary objective is to evaluate the efficacy and safety of nicotinamide mononucleotide (NMN) as a treatment for chronic insomnia.

### Trial design {8}

This trial will be carried out as a multicenter, double-blinded, randomized controlled superiority trial with a two-group parallel design. Participants (*n* = 400) will be allocated 1:1 to either oral MNM as treatment (intervention group) or to oral placebo (control group). Outcome assessments will be conducted two times for each participant: at baseline and at follow-up (day 60), as presented in Fig. 1.

**Fig. 1 Fig1:**
[figure not shown]
Study flowchart

### Eligibility criteria {10}

#### Inclusion criteria

Participants will be included if they:Age between 18 and 65 years.Clinical diagnosis of chronic insomnia (according to the ICSD-3 criteria for chronic insomnia).Without hepatorenal and cardiac dysfunction (normal laboratory examination, ECG, etc.)Can be trained and able to use the smart wearable device.Be able to read, understand, and provide written informed consent before enrolling in the study.Agree to participate for the entire study period.

#### Exclusion criteria

Patients will be excluded if they:Physical diseases, mental disorders, and/or sleep disorders (including patients with restless legs syndrome) that are clearly diagnosed, directly affect sleep, and are not cured.Received any insomnia drugs and psychotherapy within the preceding 1 month.On a continuous current daily intake of nutritional supplements and vitamin supplements.Pregnant, shift workers, perennial night shift workers, frequent cross-timezone pilots (such as crew members of international flights), and patients with sleep phase delay syndrome.Cancer, dyslexia, or lack of self-care ability.Depression and suicide risk (suicide plan/attempt within the preceding 1 month).Regular medicated background systemic chronic diseases, such as hypertension and diabetes.Hyperuricemia or gout.Sleep disorders caused by other diseases.

### Who will take informed consent? {26a}

The fully trained specific researchers who are on-site will obtain informed consent from participants.

### Additional consent provisions for collection and use of participant data and biological specimens {26b}

On the consent form, participants are asked to sign if they agree to have been given written and oral information on the purpose, method, advantages, and disadvantages of saying yes to participate in the trial, and if they agree to participate voluntarily. On the consent form, participants are informed that they can withdraw the consent without losing any rights to treatment, either current or future. They are also asked if they agree to the use of their data when they choose to withdraw from the trial.

This trial does not involve collecting biological specimens for storage.

## Interventions

### Explanation for the choice of comparators {6b}

Participants in the control group will take the oral placebo which is manufactured where same as the intervention oral NMN.

Chronic insomnia is not a life-threatening disease, instead, patient’s emotional and mental status can be contributed. The prescribed treatment for chronic insomnia primarily involves drug and behavioral treatments both have limitations, thus, to use placebo as the control group.

### Intervention description {11a}

In this trial, the intervention group (*n* = 200) will have oral MNM (320 mg/day), 1 tablet bid(each tablet contains 160 mg NMN), after the meal for 60 days. The control group (*n* = 200) will have oral placebo, 1 tablet bid, after the meal for 60 days.

### Criteria for discontinuing or modifying allocated interventions {11b}

Interventions could be discontinued or modified under the below circumstances:Allergic reactions: If allergic skin reactions have been observed, discontinue allocated interventions. Meanwhile, this should be reported as an adverse event.Headache: If headache has been observed, temporary suspension of the allocated intervention until the symptom disappears is recommended. If the headache re-happens, discontinue allocated interventions. Meanwhile, this should be reported as an adverse event.Nausea: If nausea has been observed, temporary suspension of the allocated intervention until the symptom disappears is recommended. If the headache re-happens, discontinue allocated interventions. Meanwhile, this should be reported as an adverse event.

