#### Safety outcome

The primary safety outcome s the incidence of adverse events. Physical examinations, laboratory tests and abdominal ultrasonography will be performed on baseline and after 60 days of treatment. The physical examination includes blood pressure, height, weight, and heart rate. Laboratory tests include urine routines, blood routines, liver and renal function, and ECG. Adverse events (AE) will be recorded in CRF; “adverse event record” of CRF includes adverse event occurrence time, end time, duration, severity, measurement taken, and outcome, and made judgment on the relationship between adverse events and interventions.

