### Composition of the data monitoring committee, its role and reporting structure {21a}

#### Refer to above {5d}

### Adverse event reporting and harms {22}

Participants will be monitored throughout the period of the intervention to detect any unintended events.

An adverse event refers to any untoward medical occurrence which happens during the trial. The study will monitor for the following NMN-related adverse events (AEs) will be monitored through routine follow-ups, including allergic reactions, headache, and nausea. Besides, other AEs will also be reported and recorded in CRF; “adverse event record” of CRF includes adverse event occurrence time, duration, end time, severity, measures taken and outcome, and make judgment on the relationship between adverse events and interventions. As safety outcome measures, AEs will be used to evaluate the safety of the intervention.

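### The nausea stopping rule names headache as its recurrence trigger, so the explicit instruction to discontinue on recurrent nausea is missing (minor)

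*Protocol article*

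**What the plan says.** Section {11b} of the protocol article opens with a permissive lead-in, "Interventions could be discontinued or modified under the below circumstances", and lists three circumstances.

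- **Allergic skin reactions:** discontinue.
- **Headache:** "If headache has been observed, temporary suspension of the allocated intervention until the symptom disappears is recommended. If the headache re-happens, discontinue allocated interventions".
- **Nausea:** "If nausea has been observed, temporary suspension of the allocated intervention until the symptom disappears is recommended. If the headache re-happens", followed by the same instruction to discontinue.

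Each of the three also requires the event to be reported as an adverse event.

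Elsewhere, the Safety outcome section makes "the incidence of adverse events" the primary safety outcome. Adverse event reporting and harms {22} says that the NMN-related events "will be monitored through routine follow-ups, including allergic reactions, headache, and nausea". Neither section contains a rule for stopping treatment.

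**The concern.** The headache and nausea rules are plainly meant to work alike: suspend at the symptom, resume when it clears, stop if it comes back. In the nausea rule the last step is tied to headache. A return of headache presupposes an earlier headache, and the nausea rule mentions none, so the sentence does not work as printed.

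At stake is a stopping instruction for participants taking a tablet twice daily for 60 days (Intervention description {11a}) in a multicenter trial. Nausea is one of the three events the protocol picks out for monitoring. As written, it is the only one of the three with no explicit instruction to discontinue. On-site staff would have to infer that step from the neighbouring rule.

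**Working it through.** The point is textual. No sample size, power or error-rate figure enters it, and there is no figure of the plan's own to reproduce.

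**Step 1. Set the three rules of {11b} side by side.**

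| Rule | First step | Recurrence trigger as printed | Action on recurrence |
|---|---|---|---|
| Allergic skin reactions | Discontinue | None needed | Not applicable |
| Headache | Suspend until it clears | Headache | Discontinue |
| Nausea | Suspend until it clears | Headache | Discontinue |

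**Step 2. Compare the headache and nausea rules word by word.** Counting from the label to the end of the reporting sentence, each rule has 34 words. They differ in two positions, the label and the first mention of the symptom, so 34 − 2 = 32 words are identical. The symptom is named three times in each rule (label, first step, recurrence step). In the nausea rule two of the three were changed to nausea and the third was left as headache. That is the pattern of a copied rule edited incompletely. The sentence is complete and grammatical, so PDF extraction or redaction does not explain it.

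**Step 3. Count the explicit instructions to discontinue in {11b}.**

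| Trigger | As printed | Evidently intended |
|---|---|---|
| Allergic skin reactions | 1 | 1 |
| Recurrent headache | 2 | 1 |
| Recurrent nausea | 0 | 1 |
| Total | 3 | 3 |

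**Step 4. Look for the missing instruction elsewhere.**

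- *Safety outcome* covers examinations, laboratory tests and adverse event recording.
- *Adverse event reporting and harms {22}* lists the monitored events ("including allergic reactions, headache, and nausea") and what is recorded about them.
- *Frequency and plans for auditing trial conduct {23}* covers confirming that adverse events and treatment changes are recorded.

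None of these says what to do with treatment when nausea returns.

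**Step 5. Follow the text literally for a participant whose nausea returns and who never had a headache.** The suspension step is not limited to a first episode, so it applies again. The recurrence step is not triggered, because there is no headache to return. The lead-in allows staff to stop treatment but does not direct it. The participant could be suspended repeatedly without ever meeting an explicit instruction to stop.

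**The case against.** The strongest case on the other side is that this is a typographical slip with no shown consequence.

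- **The intent is obvious.** The sentence sits under the nausea label and follows the same two steps as the rule above it. Read literally it would only duplicate the headache rule, so most readers would take it to mean nausea. This stands, and it is why the point is minor. It tells the sponsor what the correction should be; it does not make the wording right.
- **Recurrent nausea is not left without any instruction.** Suspension applies again, the lead-in permits stopping, and the event is reported. This also stands. What is lost is only the directed move from suspension to discontinuation, which the headache rule has.
- **Only a journal article is at hand.** Sites work from the full protocol, which may be correct. This limits the claim: the error is shown in the published text, not in the instructions sites followed. It does not excuse the wording, because the article has not condensed the rule or left it to another document. It prints the rule in full and gives it the wrong trigger.
- **The article has other language slips**, such as variant spellings of the product's abbreviation. Those do not change an instruction to staff; this one does.

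**Conclusion.** The concern holds, as a minor inconsistency. One wrong word in one of three rules removes the explicit instruction to discontinue when nausea recurs, and no other section restores it.

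The consequence is confined to that instruction. Nothing in the text shows that sites handled cases differently. The reporting of nausea as an adverse event is untouched, so no effect is claimed on the adverse event incidence outcome, and none on the sample size or the analysis of the Pittsburgh Sleep Quality Index.

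That the rule should stop treatment on recurrent nausea is an inference from the parallel headache rule, and a strong one given the near-identical wording. Whether the full protocol carries the same error cannot be judged from the article.

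**What to change.** In the recurrence sentence of the nausea rule in {11b}, replace *headache* with *nausea*, so that treatment is discontinued if nausea returns after a suspension. Check the same sentence in the full protocol used at sites. If it has the same wording, correct it there through the amendment route in section {25} and tell the sites.

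The cost is a one-word correction and one check of the full text. Design, conduct and analysis are unaffected.

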### Strategies to improve adherence to interventions {11c}

Adherence enhancement strategies are in use throughout the trial period, e.g., patients are being reminder of the importance of adhering regardless of allocation via phone call on day 1, day 3, day 7, day 15, day 30, day 45, and day 60.

### Relevant concomitant care permitted or prohibited during the trial {11d}

Throughout the trial period, participants regardless of allocation, who had background disease are permitted to have relevant medicines accordingly but are prohibited from taking together with the intervention. Participants regardless of allocation are prohibited from taking any treatment may impact the objective function e.g., anti-oxide, sleep improvement, visual fatigue reliving, body fatigue relieving).

### Provisions for post-trial care {30}

The trial sponsor will provide free medical treatment or make compensation/compensation according to relevant Chinese laws to fulfill the needs related to direct consequence of trial participation (e.g., intervention-related harms). The sponsor has insurance to cover for harms associated with the interventions. The insurance will cover for additional health care, compensation, or damages either provided voluntarily by the Sponsor, or by claims pursued through the standard process.

### Outcomes {12}

#### Primary outcome

The primary outcome is the mean change of score between baseline and follow-up after 60 days of treatment which indicated sleep efficiency. It will be assessed with the Pittsburgh Sleep Quality Index (PSQI) questionnaire. It includes nine items/18 questions with seven categories, including subjective sleep quality, sleep latency, sleep duration, habitual SE, sleep disturbances, use of sleep medications, and daytime dysfunction. A global sum score for the PSQI > 5 indicates poor sleep. The Cronbach’s α value for the PSQI is 0.83 [32, 33].

#### Secondary outcome

Other sleep efficiency indices, including the Epworth Sleeping Scale (ESS) and Insomnia Severity Index (ISI), the mean change of score will be used at the baseline and follow-up after 60 days of treatment for the secondary outcome assessment. The ESS consists of 8 self-rated items, each scored from 0–3, that measure a subject's habitual “likelihood of dozing or falling asleep” in common situations of daily living. No specific time frame is specified. The ESS score represents the sum of individual items and ranges from 0 to 24. Values > 10 are considered to indicate significant sleepiness. The ESS is sensitive to change in clinical status, as evidenced by improvements following treatment of sleep apnea with continuous positive airway pressure (CPAP). Ten psychometric analyses of the ESS support its internal consistency. The ISI is a 7-item self-report questionnaire that assesses the nature, severity, and impact of insomnia. The dimensions are severity of sleep onset, sleep maintenance and early morning waking problems, sleep dis- satisfaction, interference of sleep difficulties with daytime functioning, noticeability of sleep problems by others, and distress caused by sleep difficulties. It is rated on a 5-point Likert scale (total score 0–28). A score of 0–7 indicates absence of insomnia, 8–14 sub-threshold insomnia, 15–21 moderate insomnia, and 22–28 severe insomnia. Internal consistency is excellent in community as well as clinical samples (Cronbach’s alpha 0.90–0.91 [33, 34]).

Secondary outcomes also include the mean change from the baseline to follow-up after 60 days of treatment in total sleep time (TST), sleep efficiency (SE), sleep latency, REM sleep latency, the percentage of N1, N2, N3, and REM which been assessed by polysomnography (PSG, Model: NS-100A). PSG is a comprehensive study of the biophysiological changes that occur in the human body during sleep. The electrodes will be attached to each participant, recording data from electroencephalogram, eye movements electrooculogram, electromyogram muscle activity or skeletal muscle activation, heart rhythm, respiratory airflow, respiratory effort, and peripheral pulse oximetry. All PSG studies will be conducted in the participants’ own homes. Data from PSG will be analyzed by the researcher.

